### 3.6.2 Selection: control vs. intervention

Patients admitted to hospital for worsening COPD and/or CHF will be recruited by the research nurses employed in this project from Emergency or on the ward once their condition has stabilized sufficiently.

Patients will be screened against inclusion and exclusion criteria for eligibility to participate in the study. Written informed consent will be obtained. Patients will be randomized into either the control or the intervention arm 1:1. The control group will receive usual care. The intervention group will receive usual care plus a PCC nurse-led intervention. Randomization will be done through computer generated lists and stored in sealed envelopes.

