### 3.6.5 Number of patients – Power analysis

To achieve 80 % power with an alpha-error of 0.05 for an increase in the number of patients with improved self-efficacy  $> 5$  units from 20% to 40%, the number of participants in each group (comparison and intervention) needs to comprise 91 patients. We aim to include 110 patients in each group to have some margin for withdrawals/ dropouts

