### 3.9 Statistical methods and analysis

The statistical analyses will have a significance level of 5 % and, when relevant, 95 % confidence intervals will be reported. Mean values will be compared using t-tests and non-parametric tests will be used for analysis of nominal and ordinal data. Logistic regression will be used to study the co-variation of descriptive variables in relation to the results.

Regarding descriptive statistics, absolute numbers and percentages will be calculated for nominal variables; means and standard deviations will be computed for normally distributed continuous variables; and medians and quartiles will be calculated for non-normally distributed variables.

The primary outcomes in the intervention and control groups will be compared by ....

All analyses will have a significance level of 0,05 %, and 2-sided tests will be used.

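### Section 3.9 states the significance level as both 5 % and 0,05 %; the second conflicts with the alpha of 0.05 in section 3.6.5 and is very probably a slip

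*Protocol*

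**What the plan says.** Three places in the Protocol bear on the level.

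- Section 3.9, opening sentence: "The statistical analyses will have a significance level of 5 % and, when relevant, 95 % confidence intervals will be reported".
- Section 3.9, closing sentence: "All analyses will have a significance level of 0,05 %, and 2-sided tests will be used".
- Section 3.6.5, power analysis: "To achieve 80 % power with an alpha-error of 0.05", for a rise in the proportion improved from 20 % to 40 %. Each group "needs to comprise 91 patients", and the recruitment target is raised to 110 per group to cover withdrawals and dropouts.

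Both sentences in section 3.9 are current text. Each is worded to cover the analyses in general, and neither is marked as overriding the other. The closing sentence is also the only one of the three that says the tests are two-sided.

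**The concern.** The two sentences in section 3.9 differ by a factor of 100: 5 % is 0.05, while 0,05 % is 0.0005. The decimal comma alone does not explain this. Written as 0,05 with no percent sign, the figure would agree with the rest of the document, but the percent sign is printed.

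The level is the rule by which the trial's results are called significant. A p-value of 0.01, for example, passes under the opening sentence and fails under the closing one, and the protocol gives no order of precedence. The closing sentence also fits neither the 95 % intervals in its own section nor the alpha on which the trial was sized. If it were applied as printed, the planned number of patients would not give the stated power.

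**Working it through.** **Inputs.** From section 3.6.5: proportions improved p1 = 0.20 and p2 = 0.40, power 80 %, alpha 0.05, 91 per group required, 110 per group recruited. From section 3.6.2: 1:1 allocation. From section 3.9: two-sided tests, and the two candidate levels, 0.05 and 0.0005. The protocol does not say which two-proportion formula was used, so the first step is to find one that returns 91.

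**Step 1: reproduce the plan's 91 at alpha 0.05.** The difference is d = 0.20 and the mean proportion is 0.30. The null variance term is 2 × 0.30 × 0.70 = 0.42, and the alternative variance term is 0.20 × 0.80 + 0.40 × 0.60 = 0.40.

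Uncorrected: n0 = (z_alpha/2 × √0.42 + z_power × √0.40)² / d²
= (1.960 × 0.6481 + 0.8416 × 0.6325)² / 0.04 = 81.2, so 82 per group.

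With continuity correction: n = (n0/4) × (1 + √(1 + 4/(n0 × d)))²
= (81.2/4) × (1 + √(1 + 4/(81.2 × 0.20)))² = 90.9, so 91 per group.

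The stated figure is reproduced exactly by the two-sided, continuity-corrected formula at 0.05. One-sided formulas give 64, or 74 with the correction, so the 91 fits two-sided testing at 0.05.

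**Step 2: power under each level.** Power = Φ[(d − c − z_alpha/2 × √(0.42/n)) / √(0.40/n)], with c = 1/n for the continuity-corrected test and c = 0 otherwise. The critical values are 1.960 at alpha 0.05 and 3.481 at alpha 0.0005.

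At n = 91, √(0.42/91) = 0.06794, √(0.40/91) = 0.06630 and 1/n = 0.01099:

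- alpha 0.05, corrected: (0.20 − 0.01099 − 0.13315)/0.06630 = 0.843, power 80.0 %
- alpha 0.05, uncorrected: (0.20 − 0.13315)/0.06630 = 1.008, power 84.3 %
- alpha 0.0005, corrected: (0.20 − 0.01099 − 0.23647)/0.06630 = −0.716, power 23.7 %
- alpha 0.0005, uncorrected: (0.20 − 0.23647)/0.06630 = −0.550, power 29.1 %

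The same formula at n = 110, if every recruited patient were evaluable, completes the table:

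| Per group | Alpha | Corrected | Uncorrected |
|---|---|---|---|
| 91 | 0.05 | 80.0 % | 84.3 % |
| 91 | 0.0005 | 23.7 % | 29.1 % |
| 110 | 0.05 | 87.6 % | 90.5 % |
| 110 | 0.0005 | 34.4 % | 40.1 % |

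Exact binomial enumeration at 91 per group and alpha 0.0005 agrees with the approximations: 24.2 % for the chi-square test with Yates correction, 24.7 % for Fisher's exact test and 29.2 % for the uncorrected chi-square test.

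**Step 3: the sample size that 0.0005 would need.** The Step 1 formulas with 3.481 in place of 1.960 give 194.3 uncorrected and 204.2 corrected, so 195 or 205 per group for 80 % power. The planned 91 is less than half of either.

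**The case against.** The strongest reply is that the intended level is not in doubt. The opening sentence of section 3.9, the 95 % intervals paired with it and the alpha in section 3.6.5 all say 5 %, and the 91 per group reproduces exactly at two-sided 0.05. The protocol describes no multiplicity adjustment or interim analysis, and gives no reason for a stricter level. The odd figure looks like 0,05 with a stray percent sign. This stands, and it governs how the point should be read.

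A reader might infer from the closing sentence that the trial is underpowered, with 24 % to 29 % power in place of 80 %. The documents do not support that. The sample size was set at 0.05, and at that level the stated power holds. The low figures describe only what would happen if the sentence were applied literally. Quoting them as one fall from 80 % would also mix two tests: 24 % is the counterpart of 80 %, and 29 % is the counterpart of 84 %. Both assume 91 evaluable patients per group, whereas 110 are to be recruited.

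A reader might also take the closing sentence to override the opening one, since it refers to all analyses. The opening sentence is just as general, so the text gives no basis for ranking them.

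What the reply does not do is remove the error. A pre-specified decision threshold should not depend on the reader working out which of two printed values was meant.

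**Conclusion.** The contradiction is real and lies within one section: the level is given as 0.05 and as 0.0005, and only the first agrees with the power analysis. The second is very probably a slip. The sample size is not at fault; 91 per group is correct for two-sided alpha 0.05 and 80 % power.

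The size of the problem, if the closing sentence were taken literally, is a fall in power at 91 evaluable per group from 80 % to about 24 % (continuity-corrected) or from 84 % to about 29 % (uncorrected), or a power of about 34 % or 40 % with 110 evaluable per group. These figures rest on the protocol's own 20 % and 40 %, equal groups and two-sided tests. The continuity-corrected basis is inferred, because it returns the stated 91. The correction is needed because the threshold applies to every analysis, the primary one included, even though the likely intent is clear.

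**What to change.** Replace the two level statements in section 3.9 with a single sentence: *All tests are two-sided at a significance level of 5 % (alpha = 0.05), with 95 % confidence intervals where relevant.* This keeps the two-sided specification, which now appears only in the faulty sentence, and brings section 3.9 into line with section 3.6.5.

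The cost is a one-line wording correction, best made before any outcome data are analysed. The sample size, endpoints and conduct do not change.

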### 3.10 Coordination of the study

The study will be run and coordinated by the Centre for Person-centred Care (GPCC), Gothenburg University.

### 3.11 Management of data and statistics

All data will be stored, managed and be made accessible in line with PuL (Personuppgiftslagen) legislation and with Gothenburg University's guidelines on data protection.

### 3.12 Ethical considerations

|                   |                                                                                                                                                                                                                                                                                                                                                                                   |
|-------------------|-----------------------------------------------------------------------------------------------------------------------------------------------------------------------------------------------------------------------------------------------------------------------------------------------------------------------------------------------------------------------------------|
| The study         | This study will be subject to review by the regional ethics committee in Gothenburg.                                                                                                                                                                                                                                                                                              |
| The investigators | The overall responsibility for the ethical conduct of this study rests with the PI, [name].                                                                                                                                                                                                                                                                                  |
| The intervention  | The intervention consists of a conversation between patient and tele-nurse, it is as such of a purely therapeutic nature and we expect patients to benefit from the participation in the study and foresee no negative side effects.
The participants: All participants in this study will be asked to provide their written informed consent before taking part in the study. |
| The participants  | Written informed consent will be obtained from all participants included in the study. Participants may withdraw their consent to take part in the study at any point in time without any consequences.                                                                                                                                                                           |

### 3.13 Milestones

This study is scheduled to run between November 2014 and October 2015. The figure below outlines the milestones in the process.

[figure not shown]

